## Methods

### Design and setting

An investigator and assessor-blinded, parallel-group multisite randomised controlled trial (RCT) will compare a progressive balance and strengthening exercise program (*Staying UpRight*) with a low-intensity seated exercise program (*Flex and Stretch*) provided to older people living in LTC facilities located in Auckland and Hamilton, New Zealand. The study design is outlined in Fig. 1. Reporting of results will conform to the recommendations of the Consolidated Standards of Reporting Trials (CONSORT) statement [26] and to the Standard Protocol Items: Recommendations for Interventional Trials (SPIRIT) guidelines. The SPIRIT checklist is provided as Additional file 2. Any protocol amendments will be submitted to the New Zealand (NZ) Health and Disability Ethics Committee (HDEC) for review and will be updated on the trial registry.

**Fig. 1 Fig1:**
[figure not shown]
Visual presentation of the study design, including sample, assessments and interventions Abbreviations: *LTC* long-term care, *MoCA* Montreal Cognitive Assessment, *SPPB* Short Physical Performance Battery, *TUG* Timed Up and Go

### Participants

Residents aged 65 years or older within participating LTC facilities will be invited to take part. Residents who are in psychogeriatric care, respite or palliative care, acutely unwell or immobile (bed-bound) will be excluded. Study investigators will work with the LTC clinical lead to identify eligible residents. Participants will provide consent before enrolment. For residents unable to provide informed consent due to cognitive impairment, written consent will be sought from the LTC clinical manager, in accordance with NZ HDEC requirements when undertaking research amongst people with cognitive impairment.

### Randomisation

To control for LTC facility factors, randomisation will be stratified by facility and by level of care (high dependency, low dependency and dementia-level care). Levels of care in New Zealand are determined by health authority-appointed Needs Assessment Service Coordination (NASC) agencies. After baseline assessment, participants will be individually randomised to intervention (*Staying UpRight*) or control (*Flex and Stretch*) by a researcher distant from recruitment using a computer-generated random sequence.

### Outcome measures

#### Primary outcome

The primary outcome measure is fall rate (per 1000 person years).

Using the LTC facility’s incident report records, fall registers will be audited for the 6 months prior to study commencement (to provide baseline data) and for the 12 months of the study. Estimates of complete accuracy in fall ascertainment is impossible, as most falls are unwitnessed [4], but the possibility of increased falls being reported as programmes are implemented [27] will be avoided by using the already accepted and implemented reporting systems RiskMan™ (RiskMan International Pty Ltd., Southbank, Victoria, Australia) or VCare™ (VCare International Ltd., Burnside, Christchurch, NZ) that are standardised throughout all LTC facilities in the trial.

#### Secondary outcomes

Secondary outcome measures are:
*Risk of falling*, expressed as proportion of fallers per group, i.e. those who sustained at least one fall during follow-up.*Rates of hospitalisation for fall-related injury* (fracture, intracranial or extracranial haemorrhage), expressed as number of fall hospitalisations per 1000 person years of follow-up. Hospitalisation data will be collected from National Health Index (NHI) matched Ministry of Health data over 12 months.*Fall rate relative to activity exposure,* expressed as number of falls per 100,000 steps. Participants will wear a tri-axial accelerometer (Axivity AX3; Axivity, York, UK), secured on the lower back at the fifth lumbar vertebrae (L5) using a hydrogel adhesive (PALStickies, PAL Technologies, Glasgow, UK), covered with an adhesive dressing (OPSITE Flexifix™ and Hypafix™, Smith+Nephew Ltd., Watford, UK). The accelerometer is programmed to sample at a frequency of 100 Hz (range ± 8 g).*Gait volume, pattern and variability of ambulatory activity*, measured using accelerometry as described above. Algorithms are valid for gait spatio-temporal features for macro gait, i.e. volume (total steps, time spent walking, bout number), pattern of activity (bout length and bout distribution), variability of ambulatory bouts and microgait, i.e. pace, rhythm, variability, asymmetry and postural control domains of gait [28–30].*Physical performance*, measured using the Short Physical Performance Battery (SPPB) [31] and the Timed Up and Go (TUG) test [32, 33]. The SPPB comprises ability to stand for 10 s (with feet side by side, semi-tandem and tandem stance), timed chair stand (five times chair rise) and gait speed (measured over 3 m). The maximum score is 12, with higher scores indicating better function. The TUG test requires the participant to rise from a chair, walk 3 m quickly but safely to a mark on the floor, turn, walk back and sit down. A lower time indicates better function.*Cost-effectiveness* of *Staying UpRight* versus seated exercise will be estimated as both an additional cost per fall prevented and per fall requiring hospitalisation.

### Assessments

Demographic and health information (health conditions, medications, independence in activities of daily living) will be collected using a standardised Minimum Data Set (MDS 2.0; interRAI Corporation 1999) at baseline prior to randomisation. The interRAI™ (International Resident Assessment Instrument) Long-Term Care Facilities (LTCF) assessment is a standardised comprehensive observational assessment, completed on admission and 6-monthly thereafter by nursing staff for all residents in LTC.

Cognitive function will be measured at baseline and at 6 and 12 months using the Montreal Cognitive Assessment (MoCA) [34]. The MoCA comprises 16 items to assess multiple cognitive domains. A score of ≤ 10/30 is considered severe cognitive impairment, 11–18 moderate impairment, 19–23 mild and > 23/30 normal cognitive function [35].

Ambulatory activity over 7 days will be collected using the tri-axial accelerometer and data uploaded to an encrypted, secure platform (eScience Central online platform, Newcastle University, UK) [36] for storage and blinded processing.

Outcome measures will be completed at baseline and at 6 and 12 months (Fig. 2). Assessors will be trained in all aspects of participant assessment, activity monitoring and digital data management to ensure the assessments are standardised. Assessors will watch a standard assessment and each will rate the responses. Responses will be compared and discussed.

**Fig. 2 Fig2:**
[figure not shown]
Assessment schedule. *FL* facility lead, *RL* research lead, *InterRAI LTCFA* Long-Term Care Facilities Assessment, *MoCA* Montreal Cognitive Assessment, *SPPB* Short Physical Performance Battery, *TUG* Timed Up and Go

### Interventions

Both intervention and control group participants will participate in any usual activities provided in the LTC facility.

### Blinding

Assessors will be blinded to group allocation for all assessments. Group assignment will only be available to the project coordinator [name], data manager [name] and the intervention coordinator [name] and will be accessed online via a password-protected site. Participants and the staff providing the intervention cannot be blinded.

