**Methods/design:**

This is a single blind, parallel-group, randomised controlled trial with blinded assessment of outcome and intention-to-treat analysis. LTC residents (age ≥ 65 years) will be recruited from LTC facilities in New Zealand. Participants (*n* = 528 total, with a 1:1 allocation ratio) will be randomly assigned to either a novel exercise program *(Staying UpRight)*, comprising strength and balance exercises designed specifically for LTC and acceptable to people with dementia (intervention group), or a seated exercise program (control group). The intervention and control group classes will be delivered for 1 h twice weekly over 1 year. The primary outcome is rate of falls (per 1000 person years) within the intervention period.

Secondary outcomes will be risk of falling (the proportion of fallers per group), fall rate relative to activity exposure, hospitalisation for fall-related injury, change in gait variability, volume and patterns of ambulatory activity and change in physical performance assessed at baseline and after 6 and 12 months. Cost-effectiveness will be examined using intervention and health service costs.

The trial commenced recruitment on 30 November 2018.

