### Data management

All data will be stored in a confidential manner. Participants will be assigned a code which will be used for all data management and analyses. Paper data will be stored at the local site in a locked filing cabinet. Coded electronic data will be stored on a computer server at the host organisation (the University of Auckland) for the duration of the study. Access to the computer files will be password-protected and accessible only to the research team. Data quality will be monitored by the data manager on a regular basis and reported to the DMC. All project investigators will have access to the final, de-identified data set.

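### The data manager both monitors data quality and can see group assignment, and nothing says the fall data are checked without knowledge of the arm

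*Protocol article*

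**What the plan says.** Three statements in the Protocol article bear on who knows the arm while data are handled.

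- **Blinding:** "Group assignment will only be available to the project coordinator [name], data manager [name] and the intervention coordinator [name"]. Access is through a password-protected site. The same section says "Assessors will be blinded to group allocation for all assessments".
- **Data management:** "Data quality will be monitored by the data manager on a regular basis and reported to the DMC". It adds: "Participants will be assigned a code which will be used for all data management and analyses".
- **Assessments:** accelerometer data are uploaded to a secure platform "for storage and blinded processing".

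The design is described in the abstract as a "randomised controlled trial with blinded assessment of outcome and intention-to-treat analysis" and under Design and setting as "An investigator and assessor-blinded, parallel-group multisite randomised controlled trial (RCT").

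The primary outcome does not come from an assessor visit. Under Primary outcome: "Using the LTC facility’s incident report records, fall registers will be audited for the 6 months prior to study commencement", and again for the 12 months of the study. The section does not name who carries out that audit.

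**The concern.** The role that checks data quality throughout the trial is one of three roles allowed to see the allocation, and no statement suspends that access while data are being checked. The primary analysis is a ratio of fall rates, so it depends on which register entries count as falls and on each person's start and end of follow-up.

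Both can need judgement. The article itself concedes that complete accuracy in ascertaining falls cannot be reached because most are unwitnessed. Under Sample size estimation, drop-outs (35% expected) are replaced by recruitment that continues until 12 weeks before each facility finishes, so individual follow-up times will differ.

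If someone who knows the arm settles such questions, even slightly differently by arm, the shift goes straight into the primary rate ratio. Stratifying randomisation by facility cannot remove it. Participant codes do not help against a person who can look up the allocation. A secondary data stream has a stated safeguard that the primary outcome lacks.

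**Working it through.** **Text check**

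| Question | What the article states | Where |
|---|---|---|
| Who can see the arm? | Project coordinator, data manager, intervention coordinator | Blinding |
| Who monitors data quality? | Data manager, reporting to the monitoring committee | Data management |
| Who is stated to be blind? | Assessors; investigators and assessors in the design statement | Blinding; Design and setting |
| Which data are stated to be processed blind? | Accelerometer data | Assessments |
| Who audits the fall registers, and is that person blind? | Not stated | Primary outcome |

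The first two rows establish the overlap of roles. The last three show that nothing in the article limits its effect on the fall data.

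**Scale, for illustration only**

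The article gives no figure on this point. The amount of arm-dependent editing below is assumed.

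1. Inputs from Sample size estimation: control rate 2.6 falls per resident-year, 25% reduction (2.6 × 0.75 = 1.95), two-sided 5%, 90% power, 264 per group. Assume a full year of follow-up for each. Expected falls are 264 × 2.6 = 686 and 264 × 1.95 = 515.
2. Formula for the log rate ratio under a negative binomial model: n per group = (z_α/2 + z_β)² × (1/μ0 + 1/μ1 + 2k) / (ln RR)².
3. With k = 0 (Poisson) this gives 114 per group. The planned 264 is reproduced with k = 0.59, which the article does not state (k = 0.5 gives 241; k = 0.6 gives 267).
4. Removing a net fraction d of one arm's falls multiplies that arm's rate, and so the rate ratio, by (1 − d). With no true effect, SE = √[(1/2.6 + 1/(2.6(1 − d)) + 2 × 0.59)/264], and the test statistic shifts by |ln(1 − d)|/SE.

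| Net fraction of one arm's falls removed | SE of log rate ratio | Two-sided type I error |
|---|---|---|
| 0 | – | 5.0% |
| 1% | 0.086 | 5.2% |
| 2% | 0.086 | 5.6% |
| 5% | 0.086 | 9.1% |
| 10% | 0.087 | 22.8% |

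Small net shifts do little; only shifts of about 5% or more matter appreciably. Nothing in the article indicates that any such shift occurs.

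**The case against.** **The link to the primary outcome is inferred.** A reader might conclude that the trial hands the fall data to someone who knows the arm. The article does not support that. It says data quality is monitored and reported on, mentions no querying or correcting of fall records by the data manager, and names no auditor. It also relies on established incident systems standardised across facilities, which leaves less room for later discretion. This stands, and it limits the point to an opportunity for bias.

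**There may be a reason for the access.** The monitoring committee receives falls, deaths and unplanned readmissions, and formally reviews interim analyses at one meeting (Risk management and safety monitoring; Project governance). Someone may have to supply the arm. That is fair, but it need not be the role that monitors data quality, since two other roles already hold the allocation. One should not argue further that the intervention coordinator runs the class lists and the data manager therefore has no use for the code. The article gives that coordinator a monthly audit of class exercise spreadsheets and does not say who keeps the attendance registers.

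**Cleaning rules and database lock belong elsewhere.** An article may leave these to the full protocol or a data management plan, and their absence is no fault. The point rests instead on an access rule that the article does state.

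**The consequence can be overdrawn.** One can choose a borderline result and show a small shift crossing the 5% limit. At the planned effect it would not matter: a rate ratio of 0.75 with SE √[(1/2.6 + 1/1.95 + 2 × 0.59)/264] ≈ 0.089 gives |z| = 0.288/0.089 ≈ 3.2, far beyond 1.96 before any shift.

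**The larger exposure may lie upstream.** Falls come from facility incident records. Facility activities staff or trained volunteers lead the control classes, and facility staff take over the intervention classes for the second 6 months; the article says that staff providing the intervention cannot be blinded. Blinding the data manager leaves this untouched.

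**Conclusion.** The point holds as a modest one. The article expressly gives allocation access to the role that monitors data quality, and nothing says that the fall-register and follow-up data are checked or cleaned without knowledge of the arm. That sits poorly with the declared blinded outcome assessment and with the safeguard stated for accelerometry.

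Two stronger readings are not supported. One is that the primary rate ratio is biased: no arm-dependent handling is described, and its size, if any, is unknown. The other is that the sections contradict one another: the declared blinding covers investigators and assessors, and the data manager is not said to be either.

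The type I error figures rest on an assumed net loss of falls in one arm, full follow-up for all, and a dispersion of 0.59 back-calculated from the planned sample size. They show scale only. The case for acting is that the route is avoidable at almost no cost.

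**What to change.** Under Blinding, withhold allocation from the data manager, and from anyone who audits, queries or cleans fall, follow-up-time or hospitalisation data, until those data are locked. Merge the allocation only after lock.

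Where the monitoring committee needs tables by arm, have another role that already holds the allocation, the project coordinator or the intervention coordinator, supply the arm code. That role must not itself be auditing, querying or cleaning the data concerned.

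The cost is a change of access rights on the existing site and a sentence or two of text. The small downside is that the reporting task moves to another existing role.

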#### Intervention group

Participants randomised to the intervention group will attend the *Staying UpRight* program. *Staying UpRight* is a supervised balance and strength group exercise program (up to eight per group) delivered for 1 h twice weekly over 1 year. Classes will be led by a physiotherapist trained in programme delivery, supported by an assistant. Balance exercises comprise static and dynamic activities progressed by reducing hand support, reducing the base of support, reducing visual input or adding a cognitive task. The strength exercises use body weight resistance and low repetitions (2 × 10 repetitions at 5–7/10 effort) in weight-bearing positions where possible (Table 1). Exercises are progressed by increasing the number of sets, the speed or amplitude of the movement or the complexity of the task (Table 2). The programme is manualised, with exercises and progressions selected based on participants’ abilities. Exercises completed in each session and exercise progressions for the group will be recorded on a spreadsheet and reviewed as part of fidelity monitoring.

**Table 1 Tab1:** *Staying UpRight* exercises and progression principles

STRENGTH EXERCISES	
*Progression principles*	
Increase duration of static hold; increase repetition; increase number of sets; alter speed, distance moved, reduce hand support, move from sit to stand, decrease base of support (BoS)	
*Lower limb*	*Description*
Hip extension; abduction, flexion	- Stand up straight, engage core. Lower leg to floor after each movement
Lunges	- Step forwards or sideways. Bend both knees and sink towards floor. Push up with both legs to return. Repeat with alternate leg initiating step
Squats	- Standing behind chair, feet shoulder width apart, bend both knees and sink to the floor. Push up into standing. Progress by reducing hand support, increasing depth of squat, increasing speed
Sit to stand	- Standing up from chair. Progress by reducing hand support, increasing speed
Heel raises and toe raises	- Standing behind chair, lifting heels off the floor. Lifting toes off the floor.
*Upper limb*	
Breaststroke	- Hands together in front of chest. Push arms forward, pull to side & back as if doing breaststroke
Shoulder press	- Hands at shoulder level, elevating arms to ceiling through flexion. Progress from seated to standing, increase speed
Biceps curl	- Elbow flexion
Triceps chair press up	- Hands on seat of chair, back straight. Push down through arms to lift bottom off seat. Slowly bend elbows and lower
Wall press	- Stand with hands on wall at shoulder height. Keep back & legs straight, bend elbows and lower body towards the wall. Straighten elbows and return to standing
Boxing	- Jabs: make a fist punch forward alternating left & right. Hooks: make a fist and punch across your body
	- Uppercuts: Make a fist and punch upwards from waist to chin. Progress from seated to standing, increase speed
*Trunk*	
Trunk flexion, extension, side flexion, rotation	- Progress from seated to standing
BALANCE EXERCISES	
*Progression principles: static exercises*	
- Increase duration of static hold	
*Progression principles: dynamic exercises*	
- Increase or vary speed; require stop, start or change direction on command	
*Progression principles: all exercises*	
- Reduce hand support, BoS, visual input; add a cognitive task; combine exercises & progressions	
*Centre of gravity*	***Description***
Low level	- Stand with chair support both hands, one hand
	- Stand unsupported, arms by side
	- Stand arms crossed
	- Feet together; semi-tandem stance; tandem
	- Arms to side; arms crossed
Medium level I	- Reduce BoS: feet together, move to semi-tandem stand
	- Reduce sensory input: eyes closed
	- Add cognitive task: count backwards out loud
High level II	- Reduce BoS and add arm movements: unilateral to bilateral
	- Standing + throw & catch: reduce BoS + throw & catch
*Weight transfer within limits of stability*	
Low level	- Standing shift weight foot to foot
	- Standing move hips in circular figure of 8 patterns
	- Marching
Medium level II	- Nudge object on ground in different directions with foot; pass between feet and to neighbour
High level I	- Reduce BoS (feet together, semi-tandem, tandem) reach: turn & reach
	- Pass ball/object between group members; vary height & distance of reach
	- Alternating top taps forwards, backwards, sideways, diagonally
*Postural strategy: challenging limits of stability*	
Low level	- Standing sway: forwards & return to midpoint. Repeat backwards/lateral directions
	- Standing pass object (newspaper, scarf) around body
Medium level	- Standing sway forwards, backwards, sideways, diagonal *without stopping at midpoint.* Increase sway speed/distance
	- Squat and pass object between legs in figure of 8 pattern
High level	- Standing sway eyes closed
	- Step forwards, backwards, sideways, lean & step; increase speed and step length
GAIT TRAINING	
Low level	- Step forwards, backwards, sideways, diagonally
	- Walk on spot/on toes/heels
	- Turn clockwise/anticlockwise around chair
High level II	- Tandem walk forwards/backwards
	- Step over obstacles
MULTISENSORY TRAINING	
Low level (sitting)	- Fix eyes on finger: follow moving finger keep head still
	- Fix eyes on point ahead, move head slowly side to side, up & down, diagonally
	- Fix eyes on point ahead, move head slowly side to side, up & down, diagonally
	- Sit unsupported with eyes closed
Medium level II (standing)	- Stand still, eyes closed
	- Turn trunk in same direction as turning head & pass object to neighbour turning trunk in same direction as head. Swing arms/scarf with trunk & head whilst watching arms/scarf
High level	- Reduced BoS. Fix eyes on finger & track moving finger, head still
	- Reduced BoS. Fix eyes on point & move head slowly side to side, up & down, diagonally keeping eyes fixed
	- Reduced BoS, eyes closed

*Note:* The table shows selected exercises. The full programme is available on request from the corresponding author

**Table 2 Tab2:** *Staying UpRight* class structure

Weeks 1–2	5 min	Breathing control/posture
Balance	10 min	1–2 exercises from each category^a^
Strength	20 min	10 repetitions × 2 sets; 60 s rest
		Upper limb × 2–3
		Trunk × 2
		Lower limb × 3–4
Cool down	5 min	Stretching
Weeks 3–4	5 min	Breathing control/posture
Balance	10 min	1–2 exercises from each category^a^
Strength	20 min	15 repetitions × 2 sets; 60 s rest
		Upper limb × 2–3
		Trunk × 2
		Lower limb × 3–4
Cool down	5 min	Stretching
Weeks 5–6	5 min	Breathing control/posture
Balance	15 min	2–3 exercises from each category^a^ (introduce new exercises & progress previous)
Strength	25 min	12–15 repetitions × 2 sets; 60 s rest
		Upper limb × 3
		Trunk × 2–3
		Lower limb × 4
Cool down	5 min	Stretching
Weeks 7–13	5 min	Breathing control/posture
Balance	15 min	3–4 exercises from each category^a^ (Introduce new exercises & progress previous)
Strength	30 min	15 repetitions × 2 sets; 60 s rest
		Upper limb × 3–4
		Trunk × 2–3
		Lower limb × 5–6
Cool down	5 min	Stretching
Week 14–ongoing	5 min	Breathing control/posture
Balance	20 min	3–4 exercises from each category^a^ (introduce new exercises & progress previous)
Strength	30 min	15 repetitions × 2 sets; 60 s rest
		Upper limb × 4
		Trunk × 3
		Lower limb × 6
Cool down	5 min	Stretching

^a^Balance categories: centre of gravity control, weight transfer, postural strategies, gait training, multisensory

To test sustainability, the LTC facility staff (physiotherapist or physiotherapy assistant) will take over delivery of the classes for the second 6 months, ensuring continuity of the programme for 1 h twice weekly over the 12-month period. If the ongoing provision of classes is compromised within a facility, alternative funding streams will be sought.

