#### Control group

Control group participants will attend a seated group activity programme (*Flex and Stretch*) delivered for 1 h twice weekly over 1 year. Classes are led by the LTC activities staff or a volunteer trained in programme delivery. Activities comprise lower limb, trunk, upper limb, head and neck movements without resistance or progressions, e.g. seated swimming, boxing, seated marching, heel and toe tapping and seated stretches; as well as activities, e.g. balloon catch and throw, pass the parcel. The programme is manualised, with class duration for each session recorded.

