### Sample size estimation

The sample size is estimated on the primary outcome, fall rate. To detect a 25% reduction in falls, assuming a control rate of 2.6 falls per resident per year (based on pilot data), we estimate a required sample size of 264 in each group (*n* = 528; two-tailed test, a = 0.05, power = 90%). The anticipated drop-out rate is 35%, which will be replaced by recruitment at participating facilities throughout the trial. Final recruitment will stop 12 weeks prior to completion of the 12-month intervention in each facility.

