### Statistical analysis

The primary analysis will be conducted on an intention-to-treat basis using data from all randomised participants, although a ‘per protocol’ analysis of the primary outcome will also be reported.

Total number of falls, number of fallers, people sustaining a fall-related fracture or brain injury; fall rate (falls per 1000 person years); multiple fallers and number in each analysis will be reported. Prior fall-incidence rates will be calculated as number of falls/resident/year using the audited 6 months prior to enrolment.

Negative binomial regression models will be fitted to determine the incidence rate ratio (IRR) for differences in fall rates between groups both for overall follow-up time as the primary endpoint and secondarily as activity-adjusted rates. Similar negative binomial models will be built for fall injury rates; fractures and head injuries both combined and separately. Logistic regression models for fallen during follow-up or not fallen and for having fallen multiple times during follow-up or not fallen will be compared between the intervention and control groups.

All models will control for prior fall rate, level of dependency and cognition (MoCA), as these are confounding factors. Baseline data will be compared between the two groups, with any strongly imbalanced factors further adjusted for in the analysis.

Per protocol analyses will be performed including those with higher attendance, and pre-planned subgroup analyses will include those with moderate and high levels of cognitive impairment.

Fall rate relative to activity exposure will be calculated and compared between groups. Within-group change will be examined using repeated measures. Generalised linear mixed-effects regression models will be used for volume, pattern and variability of ambulatory activity and cognition.

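### Both arms are treated in group classes, but the primary falls model and the sample size make no allowance for within-class correlation; unless it is negligible, the interval is too narrow and the power overstated

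*Protocol article*

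**What the plan says.** Under Randomisation, individual residents are allocated, stratified by facility and level of care. Under Intervention group, Staying UpRight is a "supervised balance and strength group exercise program (up to eight per group) delivered for 1 h twice weekly over 1 year". Under Control group, "Control group participants will attend a seated group activity programme"; the size of the control classes is not given. The Contamination section has the two arms taught separately, by different facilitators, with attendance registers for both. Facility staff take over the intervention classes for the second six months.

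Under Statistical analysis, "Negative binomial regression models will be fitted to determine the incidence rate ratio (IRR) for differences in fall rates between groups". The listed adjustments are earlier fall rate, dependency level and MoCA score. Class, facilitator and facility do not appear, and no robust variance is named for falls. Mixed-effects models are named, but only for the activity measures and cognition.

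Under Sample size estimation, for a 25% reduction from 2.6 falls per resident-year, "we estimate a required sample size of 264 in each group" ("two-tailed test, a = 0.05, power = 90" per cent). No dispersion, ICC or design effect is stated.

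**The concern.** Individual randomisation balances what residents bring with them, including the facility they live in. It does not remove correlation that arises afterwards, when residents share an instructor, a room and companions for up to a year. A facility effect common to both arms largely cancels in the comparison. A class effect does not, because each class and its facilitator belong to one arm.

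If that correlation is not negligible, a model that treats residents as independent understates the variance of the log rate ratio. The confidence interval for the primary rate ratio is then too narrow, the 5% test rejects too often, and the stated power is too high. The Contamination section weighs clustering only as an argument against randomising whole facilities. It does not deal with correlation created by the classes.

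**Working it through.** **1. The stated sample size.** Inputs from Sample size estimation: rates 2.6 and 0.75 × 2.6 = 1.95 per resident-year, two-sided 5%, power 90%. One year of follow-up per resident is assumed.

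n per arm = (1.960 + 1.2816)² × [1/2.6 + 1/1.95 + 2k] / (ln 0.75)² = 10.507 × [0.897 + 2k] / 0.0828, where k is the negative binomial dispersion.

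- k = 0 (Poisson): 114 per arm.
- k = 0.5: 241; k = 0.75: 305.
- 264 per arm needs k ≈ 0.59 if nothing is held back for clustering.

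Since k is not given, 264 cannot be reproduced from the stated inputs. The steps below take 264 as giving exactly 90% power under independence.

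**2. Design effect.** DE = 1 + (m − 1) × ICC, with m = 8 (the stated maximum in the intervention arm, assumed for the control arm too). The ICC values are assumptions. Power of a correctly specified analysis = Φ(3.2415/√DE − 1.96). Type I error of a test that ignores classes = 2 × [1 − Φ(1.96/√DE)].

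| ICC | DE | Effective n per arm (264/DE) | Power | Type I error |
|---|---|---|---|---|
| 0.01 | 1.07 | 247 | 88.0% | 5.8% |
| 0.02 | 1.14 | 232 | 85.9% | 6.6% |
| 0.05 | 1.35 | 196 | 79.7% | 9.2% |

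With classes of six, ICC 0.02 gives DE 1.10, power 87.1% and type I error 6.2%; ICC 0.05 gives 1.25, 82.6% and 8.0%.

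**3. Simulation without a treatment effect.** Assumed layout: 33 classes of eight per arm, spread as 33 facilities with one class per arm or 11 facilities with three. Mean 2.6, k = 0.59, negative binomial model ignoring facility and class, no covariates; 2,500 trials per cell, or 6,000 where facility variance is large. With class log-variance s², ICC = μ²(e^{s²} − 1) / [μ²(e^{s²} − 1) + μ + kμ²e^{s²}]. Here s² = 0.01, 0.02 and 0.05 give ICCs of about 0.010, 0.020 and 0.049.

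The large facility variance comes from the facility rates of 0.68 to 7.67 quoted under Contamination, read as a span of 4 SD: ln(7.67/0.68)/4 = 0.606, variance 0.37. Ranges are over the two layouts.

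| Class log-variance | Type I error, no facility variance | Type I error, facility log-variance 0.37 |
|---|---|---|
| 0 | 4.5–5.0% | 3.3–3.7% |
| 0.01 | not run | 4.4–4.5% |
| 0.02 | 5.9–7.0% | 5.2–5.8% |
| 0.05 | 9.6% | 7.4–8.2% |

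Leaving out a strong stratification factor makes the test conservative, which offsets a small class effect.

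**4. The planned adjustment for earlier falls.** A further simulation (33 facilities, one class of eight per arm, k = 0.5, 1,200 trials per cell) added a six-month prior fall count. The two figures are for facility log-variances 0.25 and 0.37.

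- No class effect: 4.8% and 4.6%, against 3.3% and 3.3% without the covariate.
- Class log-variance 0.0225 (ICC about 0.025): 7.4% and 5.8%.
- Class log-variance 0.05 (ICC about 0.05): 10.2% and 9.5%.

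Earlier falls carry facility information, so this covariate removes most of the conservatism seen in step 3.

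**The case against.** The strongest counter-argument is that the model as written starts out conservative, because it omits facility, and facility rates may differ more than tenfold. Without covariates, this roughly cancels a class ICC of 0.01 and nearly cancels one of 0.02. It stands as a limit on size, but the planned covariate takes much of the protection away (step 4).

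Second, the mechanism may be weak. Nothing says that class membership is fixed, and turnover is expected: "The anticipated drop-out rate is 35%, which will be replaced by recruitment at participating facilities throughout the trial". Attendance in the pilot was 60%. The programme is manualised and tailored to each participant's ability. Control classes involve no progression and may carry little class effect; with class variation in the intervention arm only, type I error at class log-SD 0.15 was about 5%. The number of facilities, classes per facility and control class size are all unstated. These points bear on the size of the ICC and justify showing a range.

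Third, 264 exceeds the Poisson requirement of 114, so some margin for clustering cannot be excluded. The text claims none.

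Fourth, a condensed article may leave variance estimation to the analysis plan. Here, however, the article fixes the primary model and its covariates, and names mixed models for other outcomes only.

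A reader might infer that type I error reaches 11% to 15%. Values of that order need class log-SDs of about 0.25 to 0.35. At k = 0.5 these correspond to ICCs of about 0.07 and 0.12, beyond the 0.01 to 0.05 used for power, and nothing in the document supports clustering that strong.

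**Conclusion.** The point holds conditionally. Treatment is delivered in arm-specific groups, the primary model has no class or facility term, and the sample size states no design effect. Unless the within-class ICC is about 0.01 or less, the primary interval will be too narrow and 90% power too high. For ICC 0.01 to 0.05 and classes of eight, power is about 88% to 80% and type I error about 5% to 10%, with the lower end applying when facility variance is large and facility is omitted.

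This rests on an assumed ICC, equal class size in both arms, reasonably stable class membership and no hidden margin in 264. Two stronger readings are not supported. The document does not show that the interval is certainly too narrow, since it gives no ICC. Nor does the wide spread of facility rates by itself inflate the error; under stratified individual randomisation it works in the opposite direction.

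**What to change.** - Fit the primary falls model with facility, the stratification factor, and a random intercept for class within facility and arm, entered together. Facility alone would remove the conservatism and leave the class effect uncovered. Alternatively, use standard errors clustered by class with a small-sample correction.
- Define class membership from the attendance registers, with a rule for residents who join late or change class.
- Restate the power of the 528 participants over a stated ICC range, with the dispersion and class size assumed in each arm. This does not require enrolling more residents.

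The cost is analysis wording, settled before unblinding; the registers are already planned. The downside is a slightly wider interval and a lower stated power. If class correlation proves negligible, little precision is lost.
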